### Sample Size

This study represents the first application of Gold Needle intervention for the treatment of aMCI. Due to the absence of comparable studies in this domain previously, an accurate estimation of the sample size parameters was not feasible. This study seeks to undertake an exploratory RCT. This study took a group of patients with MCI as the research subjects. In accordance with the sample size recommendations for preclinical trials in traditional Chinese medicine and taking into account parameter precision, a total of 90 participants were selected, comprising 30 individuals in the Gold Needle “Regulating Spirit” group, 30 in the general acupuncture “Regulating Spirit” group, and 30 in the sham acupuncture control group.

### Statistical Analysis

Quantitative data were statistically described using SPSS 21.0 software (IBM Corp) and presented as mean (SD; x±s). Three sets of continuous variable statistics were analyzed: Based on the distribution characteristics of the data, comparisons among groups of continuous variables were conducted using either ANOVA or the Kruskal-Wallis H test. In cases where a statistically significant overall difference was identified among the 3 groups, post hoc multiple comparisons were performed using either the least significant difference test or the Nemenyi test. Baseline data, along with data collected at week 12 and follow-up data at 24 weeks, were analyzed using repeated measures ANOVA or generalized linear mixed models tailored for repeated measures.

The brain structure images acquired through MRI will be processed using MATLAB (MathWorks) [26], CAT12 (Computational Anatomy Toolbox; C. Gaser, Structural Brain Mapping Group, University of Jena, Germany) [27], and FSL (FMRI Software Library 5.0; Analysis Group, FMRIB, University of Oxford, United Kingdom). We used 2 distinct analytical approaches, namely voxel-based analysis and tract-based spatial statistics, to assess alterations in total gray and white matter volumes as well as white matter fiber tracts in a patient with aMCI.

Resting-state functional MRI data will be processed using version 2.3 of the WFU_PickAtlas, developed by the Functional MRI Laboratory at Wake Forest University School of Medicine, which is designed to extract the hippocampal region of interest. Use Conn [28] for data preprocessing and statistical analysis. Use the Conn (McGovern Institute for Brain Research) and SPM12 software (Wellcome Centre for Human Neuroimaging) to perform statistical analysis of the results, including functional connectivity, regional homogeneity, and amplitude of low-frequency fluctuations indicators, and visualize the nodes in 3D using the BrainNet Viewer [29] software.

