## Methods

### Study Design

This study is designed as a randomized controlled trial (RCT) using block randomization. We will recruit 90 participants diagnosed with aMCI and allocate them into 3 groups in a 1:1:1 ratio; specifically, the Gold Needle “Regulating Spirit” group, the general acupuncture “Regulating Spirit” group, and a sham acupuncture control group. Additionally, we will include 20 healthy volunteers to serve as a control group. The participants’ gender, age, and educational background will be aligned with those of the patients with aMCI. A total of 90 patients with aMCI will undergo treatment for 12 weeks in groups, receiving interventions 3 times per week. Data collection for all enrolled individuals will occur at baseline (week 0), week 12, and week 24.

The study protocol has been registered in ClinicalTrials [18]. The flowchart of the trial is shown in Figure 1 and the research content at different periods of the trial is given in Table 1.

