### Randomization, Allocation Concealment, and Blinding

This study used a block-randomized design, wherein an independent statistician—who was not involved in trial assessment, treatment allocation, or statistical analysis—generated the randomization sequence using SAS 9.2 (SAS Institute) software’s PROC PLAN (with a block length of 6). An independent research assistant ensured allocation concealment through the use of opaque, sealed envelopes. In this study, the acupuncturist, outcome evaluator, and data analyst were assigned by different individuals to ensure objectivity; both patients and evaluators remained blinded throughout the process. Given the unique nature of Gold Needle manipulation, challenges arose in establishing acupoint settings for the sham group and in maintaining blinding for the acupuncturist. To address these issues, we strictly adhered to patient blinding protocols and scheduled individual appointments at staggered times.

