## Results

This study was initiated on September 1, 2023. As of October 30, 2025, 110 eligible participants had been enrolled, and data collection had been completed in full. Data analysis is currently underway, and the preliminary results are expected to be available by June 2025. We hypothesize that, compared with the general acupuncture “Regulating Spirit” group, the Gold Needle “Regulating Spirit” group will demonstrate superior efficacy in improving cognitive impairment. This superiority will be reflected in multiple key outcome measures, including MoCA and Mini-Mental State Examination scores, plasma biomarkers, and functional MRI findings.

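### The test for group comparisons is picked from the observed distribution, which can also change the gold versus general threshold, and no route is named as primary for MoCA

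*Protocol article*

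**What the plan says.** The Statistical Analysis section of the protocol article contains three either/or choices.

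- **Overall test.** "Based on the distribution characteristics of the data, comparisons among groups of continuous variables were conducted using either ANOVA or the Kruskal-Wallis H test". The observed distribution is the only basis given. No normality test, threshold, or choice between a pooled and a per-arm check is stated.
- **Pairwise test.** After a significant overall result among the three groups, "post hoc multiple comparisons were performed using either the least significant difference test or the Nemenyi test".
- **Repeated data.** The baseline, week-12 and week-24 data "were analyzed using repeated measures ANOVA or generalized linear mixed models tailored for repeated measures". No basis for choosing is given.

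The primary outcome is MoCA, which Table 1 schedules at weeks 0, 12 and 24. The Results section states the hypothesis that gold needles are superior to general acupuncture. No sentence says whether the cross-sectional or the repeated-measures route decides that comparison.

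On blinding, the section on randomization, allocation concealment and blinding says that "both patients and evaluators remained blinded throughout the process". About the analyst it says only that "the acupuncturist, outcome evaluator, and data analyst were assigned by different individuals to ensure objectivity". The Results section reports that data collection is complete: "Data analysis is currently underway, and the preliminary results are expected to be available".

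**The concern.** A test chosen from the outcome data makes the verdict depend on a preliminary check that is not itself of interest. MoCA is an integer score, so a normality check can reject because of rounding or chance even where a linear model is adequate at 30 per arm.

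The choice matters here because the two branches are not equally strict. LSD makes no further adjustment once the overall test is significant, while Nemenyi is adjusted for all pairs. The two branches also answer different questions, one a difference in means and the other a shift in ranks.

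A separate gap concerns the order of the routes. Cross-sectional and longitudinal analyses can give different answers on the same MoCA data, and the article does not say which one counts. Analysis is already under way, so both choices are live. At stake is a stable, interpretable gold versus general estimate. The Discussion wants the trial to support later large trials, and they will need that estimate.

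**Working it through.** **Inputs from the article.** There are 90 patients ("a total of 90 participants were selected"), and the plan is to "allocate them into 3 groups in a 1:1:1 ratio", so n = 30 per arm and N = 90.

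**Assumptions.** The article gives no alpha, SD, effect size or visit correlation. I assume two-sided 0.05; MoCA rounded to integers and capped at 30, mean 22 in the reference arm, SD 3; and a visit correlation of 0.65. I also assume that LSD follows ANOVA and Nemenyi follows Kruskal-Wallis, the natural pairing, although the text does not spell it out. The sample size section gives no power calculation to reproduce.

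**Step 1: strictness of each branch.**
- LSD: critical t on 90 − 3 = 87 df is 1.99, so per-comparison p<0.05. The difference needed is 1.988 × √(2/30) = 0.51 SD.
- Nemenyi: critical z = q(0.95; 3, ∞)/√2 = 3.314/1.414 = 2.34, so per-comparison p<0.019. The chi-square form uses √5.99 = 2.45, p<0.014.

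**Step 2: power for gold versus general.** Simulated, 20,000 trials per scenario; each branch is a significant overall test followed by its post hoc test; sham is 0.5 SD below general.

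| True gold − general | ANOVA/LSD | Kruskal-Wallis/Nemenyi | Branches disagree |
|---|---|---|---|
| 0.74 SD | about 81% | about 59% | 21–22% |
| 0.5 SD | 47–48% | 27% | about 21% |

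**Step 3: where the gap comes from.** At 0.74 SD, Kruskal-Wallis followed by an *unadjusted* rank contrast has 74% power. Moving to ranks therefore costs about 6 points (80 to 74), and Nemenyi's adjustment costs about 15 or 16 more (74 to 58 or 59).

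**Step 4: the rule applied mechanically.** With Shapiro-Wilk at 0.05, a pooled-residual check sends about 8% of these trials to the rank branch, and a per-arm check about 26%. At 0.74 SD the resulting power is about 79% (pooled) or 75% (per arm), against 80–81% for ANOVA/LSD alone. The loss is about 1 to 5 points.

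**Step 5: direction.** It is not fixed. With skewed (gamma) data, gold 0.5 SD better and general equal to sham, Nemenyi is significant in 45% of trials and LSD in 40%.

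**Step 6: false positives for gold versus general, with no true difference between them.**
- Both better than sham by 0.8 to 1.5 SD, normal data: LSD 5.0%, Nemenyi 0.6–1.4%. Taking whichever is significant gives at most 5.0% (4.8% with rounded scores, 4.8% with skewed data).
- Sham 0.5 SD lower, rounded MoCA: taking either branch gives about 4.4%.
- Adding ANOVA on change from baseline as a third permitted route gives 8.4–8.6%, and about 8% to 9.5% over visit correlations of 0.5 to 0.8 and sham deficits of 0.5 to 0.8 SD. The article does not name change-score ANOVA; it stands in here for the repeated-measures route.

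The ANOVA/rank choice therefore adds almost nothing to the error rate. Any inflation comes from leaving the cross-sectional and longitudinal routes unranked.

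**Step 7: one fixed contrast.** At two-sided 0.05, before any gain from baseline adjustment and by normal approximation, power is 21% at 0.3 SD, 49% at 0.5 SD and 87% at 0.8 SD. For 80% power the difference must be (1.960 + 0.842) × √(2/30) = 0.72 SD.

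**The case against.** The strongest reply is that this is detail an article leaves to the full protocol or analysis plan. A basis for the choice is named, its criterion may be written elsewhere, and a rule followed mechanically costs little power. The MoCA and clinical-scale data at weeks 0, 12 and 24 are assigned to repeated-measures methods, so the LSD/Nemenyi pair may never decide the primary comparison. The trial also describes itself as exploratory.

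Much of this stands. It limits the size of the point and rules out several stronger readings:

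- A reader might infer that the data-driven choice governs every continuous outcome. It does not: repeated data and imaging have their own routes.
- A reader might infer an unblinded analyst choosing the branch. The article is silent on whether the analyst sees the arms, and it separates that role from treatment and assessment.
- A reader might infer that switching between ANOVA and ranks inflates the error rate. Step 6 shows that it does not, because with three groups LSD after a significant overall F test holds at about 5% and Nemenyi is stricter.
- A reader might call the choice discretionary. The text supports only that it depends on the data, with no criterion stated.

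The reply does not remove the stated rule itself. An analysis plan could supply a threshold, but the test would still be picked from outcome data. Nor does the exploratory label settle the matter, since the Conclusions expect a definitive answer on the gold needle's advantage.

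**Conclusion.** The point holds in a limited form. The article fixes a data-dependent choice of test. Under the natural pairing, that choice also moves the gold versus general threshold from about p<0.05 to about p<0.019. Under the assumed inputs the branches differ by about 22 points of power at 0.74 SD (81% against 59%) and disagree in roughly one trial in five. Most of that gap is multiplicity adjustment rather than ranking, and with skewed data the advantage can reverse. In routine use the rule loses about 1 to 5 points.

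The harm is an unstable verdict and an undefined primary analysis. An error rate of about 8% arises only if the cross-sectional and longitudinal routes are both left open, and that figure rests on an assumed change-score analysis. Whether the analyst is blinded is unstated and needs clarifying; no breach is shown. Because the trial is described as exploratory, this is a correction worth making rather than a threat to the design.

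**What to change.** 1. For MoCA and the clinical scales, delete the opening condition that ties the choice of test to the data's distribution.
2. Name one primary analysis: a baseline-adjusted linear or mixed model of week-12 MoCA, with one gold versus general contrast and its 95% CI, used whatever a distribution check shows. This also settles which of the cross-sectional and longitudinal routes is primary.
3. Keep Kruskal-Wallis and Nemenyi as labelled sensitivity analyses.
4. State that the analyst works with arms coded A/B/C until the programs are frozen. If analysis with the arms visible has already begun, report that, so that the choice is not presented as made blind.

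The cost is a few sentences and a recoded arm variable. The one downside is that a rank-based result can no longer serve as the main result.

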**Results:**

This study was initiated on September 1, 2023. As of October 30, 2025, 110 eligible participants had been enrolled, and data collection had been completed in full. Data analysis is currently underway, and the preliminary results are expected to be available by June 2025. We hypothesize that, compared with the filiform needle-based mind-regulating acupuncture group, the golden needle-based mind-regulating acupuncture group will demonstrate superior efficacy in improving cognitive impairment. This superiority will be reflected in multiple key outcome measures, including Montreal Cognitive Assessment and Mini-Mental State Examination scores, plasma biomarkers, and functional magnetic resonance imaging findings.

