### Outcome Assessment

The variables examined in this study encompass both demographic and clinical characteristics, as well as the primary and secondary outcome measures. The fundamental characteristics of each group were assessed at baseline (wk 0). The primary and secondary outcome measures were evaluated at baseline, at the conclusion of the intervention (wk 12), and again at 24 weeks post follow-up.

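### The stated hypothesis, gold needle versus general acupuncture, has no planned contrast and no lead MoCA visit, and its only described pairwise test waits on a three-group test that includes sham

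*Protocol article*

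**What the plan says.** The hypothesis is a single two-arm contrast. The Abstract says that "compared with the filiform needle-based mind-regulating acupuncture group, the golden needle-based mind-regulating acupuncture group will demonstrate superior efficacy", and the Results section repeats that, against general acupuncture, "the Gold Needle “Regulating Spirit” group will demonstrate superior efficacy in improving cognitive impairment". Sham has no part in it.

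The Statistical Analysis section begins elsewhere. It says "comparisons among groups of continuous variables were conducted using either ANOVA or the Kruskal-Wallis H test", the choice resting on the data's distribution. Pairwise tests then follow conditionally: "In cases where a statistically significant overall difference was identified among the 3 groups, post hoc multiple comparisons were performed". The method for this step is left open between two procedures, LSD and Nemenyi. The visit for this analysis is not given.

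The same paragraph adds that the baseline, week 12 and week 24 data "were analyzed using repeated measures ANOVA or generalized linear mixed models tailored for repeated measures". It states no contrast, no visit and no gate for that model, and does not say whether it or the three-group test decides the primary question.

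Primary Outcomes names MoCA without a time point. Outcome Assessment says the outcomes were "evaluated at baseline, at the conclusion of the intervention (wk 12), and again at 24 weeks post follow-up", and Table 1 shows MoCA at weeks 0, 12 and 24. Neither post-baseline visit is marked as primary.

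**The concern.** The question and the described test do not match. Under the pairwise route, whether gold is compared with general acupuncture depends partly on where the sham mean falls, although sham is not in the hypothesis. A real gold-versus-general difference can go untested because the overall test misses. Conversely, an overall result driven by sham does not answer the question.

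The two follow-up tests also differ in strictness. LSD is unadjusted once the gate is passed, while Nemenyi is adjusted for all three pairs. Which one applies to the primary outcome is settled by the data.

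Finally, with two post-baseline visits and two analysis routes, and no stated precedence, the article does not fix which result counts as the primary one.

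**Working it through.** **Inputs from the article.** 30 patients per arm (Sample Size) and 1:1:1 allocation (Study Design). The article gives no alpha, power, effect size or SD, so its total of 90 can be neither reproduced nor refuted.

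**Assumptions.** Normal outcomes with SD 1, two-sided 5%, no dropout, pooled three-arm variance on 3 × 30 − 3 = 87 df, and d the true gold-minus-general difference in SD units.

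**Reference for the direct test.** Power ≈ Φ(d√(30/2) − 1.96). At d = 0.5: Φ(0.5 × 3.873 − 1.96) = Φ(−0.02) ≈ 0.49. The t test on 87 df gives 0.48 by simulation. The difference detectable with 80% power is (1.96 + 0.842) × √(2/30) ≈ 0.72 SD. A difference of 0.5 SD would need 2 × (2.802)²/0.25 ≈ 63 per arm.

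**Power with the gate (simulation).** The gated LSD counts as positive only if the three-group F test and the gold-versus-general t test both reach 5%. The gate can therefore only lower power.

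| d | Sham position | Direct | F gate, then LSD |
|---|---|---|---|
| 0.5 | equal to general | 0.48 | 0.40 |
| 0.5 | midway between general and gold | 0.48 | 0.36 |
| 0.5 | 0.25 SD below general | 0.48 | 0.46 |
| 0.5 | 0.5 SD below general | 0.48 | 0.48 |
| 0.74 | equal to general | 0.81 | 0.77 |
| 0.74 | midway | 0.81 | 0.70 |
| 0.74 | 0.5 SD below general | 0.81 | 0.81 |

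Over d = 0.3 to 0.8 the LSD loss is 3 to 8 points if sham equals general or gold, 8 to 13 points if sham is midway, and at most 0.5 points if sham is 0.5 SD or more below general.

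For Kruskal-Wallis then Nemenyi at d = 0.5, rank-based simulation gives 0.30 (sham equal to general), 0.30 (midway) and 0.27 (0.5 SD below). A gated studentized-range approximation gives 0.32-0.33. This branch loses power in every scenario examined.

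With d = 0.5 and sham 0.5 SD below general, the overall test is significant in about 94% of trials, yet gold versus general is detected in 48% (LSD) or 27% (Nemenyi). Passing the gate says little about the hypothesis.

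**False positives over two visits.** This applies only if weeks 12 and 24 are each tested separately, which the article does not say. With gold equal to general, and between-visit correlation 0.5 and 0.8 (assumed), the chance of a gated LSD finding at either visit is:

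- sham equal to general: about 4-5%;
- sham 0.25 SD lower: 6.2% and 5.2%;
- sham 0.5 SD lower: 8.2% and 7.2%;
- sham 0.8 SD lower: about 9% and 8%.

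On the Nemenyi branch it stays at about 2-3%. For comparison, two independent ungated tests give 1 − 0.95² = 9.75%.

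**The case against.** The strongest reply has five parts.

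- **A second route exists.** A reader might infer that the hypothesis is tested only if the three-group test is significant. The article does not support that, because the repeated-measures or mixed model carries no stated gate. This stands. But that model comes without a contrast, a visit or precedence over the gated test, so it does not yet supply the missing primary test.
- **Two separate visit tests are an inference.** A reader might conclude that the plan runs at an 8-9% error rate. The article does not say at which visit the three-group test is done, and that rate belongs to an ungated test at both visits. With the gate it is approached only on the LSD branch with sham clearly worse. This stands, and the error figures above are conditional.
- **The gate is a recognised procedure.** With exactly three groups, LSD after a significant F test holds 5% across the pairs within one visit. This stands: unadjusted LSD is not itself a type I error fault here.
- **The harms largely exclude each other.** On the LSD branch, where the gate costs power it also restrains the two-visit error, and where it is nearly always open the power loss vanishes. The largest loss needs sham to outperform general acupuncture, contrary to the trial's premise. This also stands, so the two losses should not be added.
- **The trial is called exploratory, and detail may sit in an analysis plan not shown.** This softens the point. It does not remove it: the article states the gating rule outright, and its Conclusions promise a definitive answer on gold needles. The visit also belongs to the definition of the primary outcome.

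Sample size costs more power than the gate does. That is true, but it is no reason to accept an avoidable further loss.

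**Conclusion.** The point holds in a limited form. The article's one stated hypothesis has no planned contrast and no lead visit. Its only described pairwise test is post hoc behind a three-group test, with a data-dependent choice between two tests of unequal strictness.

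At an assumed 0.5 SD, the cost under LSD ranges from nothing to about 12 points of power (48% to 36%), depending on sham. Under Nemenyi it is roughly 15 to 21 points (48% to 33-27%). A raised error rate of 7-9% arises only if the visits are tested separately, LSD is used and sham lies about 0.5 SD or more below general. With all arms equal it is about 4-5%.

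All these figures rest on assumed effect size, alpha, normality, no dropout and between-visit correlation, since the article gives none. The mismatch between hypothesis and test does not depend on them. The matter should be settled, but it does not invalidate the trial.

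**What to change.** Name gold versus general acupuncture on MoCA at one stated visit (for example week 12, the end of treatment) as the single primary contrast, two-sided 5%. Take it from the longitudinal model already planned, and test it whatever the three-group comparison shows. Do not apply the overall-test gate or the LSD/Nemenyi switch to this primary test. Report gold versus sham, general versus sham and the other visit as secondary estimates with 95% confidence intervals.

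The Results section says that data collection is complete and analysis is underway. The choice should therefore be fixed before arms are compared and declared as a dated late change; it is credible only on those terms.

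The text itself is about one paragraph. The real cost is that the sham comparisons and the other visit become secondary.

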### Primary Outcomes

The Montreal Cognitive Assessment (MoCA) was used to assess the patients’ overall cognitive function [19]. MoCA encompasses several cognitive domains, including Visuospatial or Executive Function, Attention and Calculation, Naming, Delayed Recall, Orientation, Language, and Abstract Reasoning. The total score ranges from 0 to 30 points, with higher scores indicating superior functionality.

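### No stated MoCA analysis adjusts for the baseline MoCA score already collected, so precision is lost, though no bias results

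*Protocol article*

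**What the plan says.** All statements are in the protocol article.

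- **Outcome.** Primary Outcomes names one measure: "The Montreal Cognitive Assessment (MoCA) was used to assess the patients’ overall cognitive function".
- **Timing.** Study Design: "Data collection for all enrolled individuals will occur at baseline (week 0), week 12, and week 24". Table 1 schedules MoCA at all three visits.
- **Between-group method.** Statistical Analysis: "comparisons among groups of continuous variables were conducted using either ANOVA or the Kruskal-Wallis H test". Least significant difference or Nemenyi tests follow if the overall test is significant. No covariate is named.
- **Longitudinal method.** The same section: "Baseline data, along with data collected at week 12 and follow-up data at 24 weeks, were analyzed using repeated measures ANOVA". The sentence then offers generalized linear mixed models as the alternative. Baseline is listed with the follow-up values as data to be analysed under both options.
- **Size.** Study Design: "We will recruit 90 participants diagnosed with aMCI and allocate them into 3 groups in a 1:1:1 ratio", which gives 30 per arm. Sample Size says that "an accurate estimation of the sample size parameters was not feasible" and describes the trial as an exploratory RCT.

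The article mentions no ANCOVA, no baseline covariate and no model in which the arms share a common baseline mean.

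**The concern.** Baseline MoCA is measured before treatment, so it carries no treatment effect, but it predicts later MoCA. Used as a covariate, it removes between-patient variation from the comparison of arms. A group comparison without it leaves all of that variation in. Treating baseline as a further response, with a free mean in each arm, removes only part: the group-by-time contrast for one visit is then a change score, which subtracts the whole baseline value instead of the fraction that predicts follow-up.

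The stated hypothesis (Results) is that the Gold Needle group does better than the general acupuncture group, a comparison of 30 with 30. The sample size was not derived from a power calculation, and the Results section says enrolment and data collection are finished. Precision can therefore no longer come from more patients. The choice of model is one of the few means left to narrow the interval.

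**Working it through.** **Inputs from the article.** 30 patients per arm; MoCA at baseline, week 12 and week 24; main comparison gold versus general acupuncture. The article gives no effect size, SD, alpha or power, so its total of 90 cannot be reproduced by a power calculation and there is no planned figure to check against.

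**Assumptions.** Equal SDs at baseline and follow-up; baseline-to-follow-up correlation r = 0.5, 0.6 or 0.7; true difference 0.5 SD; two-sided alpha 0.05; no gate by the overall three-group test in any of the power figures.

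**Step 1. Variance of a two-arm contrast at one visit, in units of the unadjusted variance.**

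- Unadjusted ANOVA: 1
- Baseline as a response (change contrast): 2(1 − r)
- ANCOVA: 1 − r²

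| r | Unadjusted | Change | ANCOVA | Unadjusted ÷ ANCOVA = 1/(1 − r²) | Change ÷ ANCOVA = 2/(1 + r) |
|---|---|---|---|---|---|
| 0.5 | 1 | 1.00 | 0.75 | 1.33 | 1.33 |
| 0.6 | 1 | 0.80 | 0.64 | 1.56 | 1.25 |
| 0.7 | 1 | 0.60 | 0.51 | 1.96 | 1.18 |

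The excess variance over ANCOVA is thus 33 to 96% unadjusted and 18 to 33% for the change contrast. A simulation with three arms of 30 (10,000 runs) gave 0.99, 0.98 and 0.74 at r = 0.5, and 1.00, 0.60 and 0.52 at r = 0.7, in agreement with the formulas.

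**Step 2. Power.** Noncentrality = 0.5 × √(30/2) / √variance = 1.936 / √variance, referred to a noncentral t with 58 degrees of freedom.

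| r | Unadjusted | Change | ANCOVA |
|---|---|---|---|
| 0.5 | 48% | 48% | 59% |
| 0.6 | 48% | 57% | 66% |
| 0.7 | 48% | 69% | 76% |

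The one further degree of freedom that ANCOVA spends on the slope does not change these rounded values.

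**Step 3. The same gain in patients.** 30/(1 − r²) = 40, 47 and 59 per arm. An unadjusted comparison would need that many to match ANCOVA with 30.

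**Step 4. Direction.** For any r strictly between 0 and 1, 1 − r² is below 1. It is also below 2(1 − r), because 2(1 − r) − (1 − r²) = (1 − r)². Only the size of the loss depends on the assumed r.

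**The case against.** **The text does not tie MoCA to a single-visit ANOVA.** This is correct. The ANOVA sentence covers continuous variables in general and names neither MoCA nor a visit. The sentence that names the three visits assigns them to the longitudinal methods. The larger loss (33 to 96%) therefore applies only if the ANOVA is used for MoCA at a visit; the longitudinal route loses 18 to 33%.

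**A mixed model is already allowed.** It is, and it would retain patients who miss a visit. If it constrained baseline means to be equal across arms, it would recover about the precision of ANCOVA. The article does not exclude that form but does not state it. As worded, baseline is simply one of the responses.

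**Averaging the two follow-up visits narrows the gap in power.** Under compound symmetry with a sustained effect, the contrast of baseline with the average of weeks 12 and 24 has variance 1.5(1 − r) and power 69 to 81% for r = 0.6 to 0.7, slightly above single-visit ANCOVA (66 to 76%). That is not a like-for-like comparison. ANCOVA on the same average has variance (1 + r)/2 − r² and power 82 to 89%, so adjustment still wins.

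**Dilution of the group effect.** A reader might infer that the repeated-measures group main effect is the treatment test. A sustained effect d would then become (0 + d + d)/3, two thirds of its size, and 0.5 SD would shrink to 0.33 SD, with power of about 29 to 32% at r = 0.6 to 0.7. The article does not say this, and group-by-time is the usual test when baseline is a response.

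**Loss of patients.** A reader might also infer a large complete-case loss. Repeated-measures ANOVA does usually drop anyone with a missed visit, but the article gives no missing-data rate and reports data collection as complete. No figure for that loss can be supported.

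**Exploratory trial, unseen analysis plan.** Sample Size does say "This study seeks to undertake an exploratory RCT", and covariates are often left to an analysis plan. That tempers the severity. It does not remove the point, because the article itself states the methods and treats baseline as a response.

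**Conclusion.** The point holds as a loss of efficiency. Neither the group comparisons nor the longitudinal analysis is stated to adjust for baseline MoCA. With a correlation of 0.5 to 0.7, assumed because the article gives none, that costs 18 to 33% extra variance on the longitudinal route for a single visit, and 33 to 96% if an unadjusted ANOVA is used. At an assumed 0.5 SD, ANCOVA would bring power to 59 to 76%, against 48 to 69% and 48% respectively. The direction holds for any correlation between 0 and 1.

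It would be wrong to conclude that the planned comparisons are biased: randomisation protects all of them. The change is worth making but is not a matter of validity.

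**What to change.** Name one primary MoCA analysis for the three randomised arms: a linear mixed model with weeks 12 and 24 as responses; arm, visit and arm-by-visit as fixed effects; and baseline MoCA with baseline-by-visit as covariates. A mixed model that keeps baseline as a response but constrains its mean to be equal across arms is an acceptable equivalent. Report the gold minus general adjusted mean difference at week 12 with its 95% CI.

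Choose the mixed model and drop repeated-measures ANOVA as an alternative, so that patients who miss one follow-up visit still contribute. For the Functional Activities Questionnaire, the two Hamilton scales and the plasma markers, use ANCOVA at week 12 with the baseline value as covariate.

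No new data are needed: Table 1 already schedules these measures at baseline, and a mixed model is already among the permitted methods. Because the Results section says analysis is underway, the change should be recorded with a date before any comparison between arms is seen. That is the only cost.
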